### Quasi-Experimental Field Study

A randomized controlled trial is generally considered as the gold standard in evaluative health-related research, as causal inferences about the therapy under study can be drawn [27]. However, in this project, there are several practical and ethical issues that do not allow for such a design. Most importantly, a precondition set by the participating organization was that their management would select 2 preexisting departmental units for the study and that both units would receive the intervention. However, a control group is needed to distinguish between the change in the outcome over time due to the planned intervention or to evaluate the changes over time due to unmeasured or unknown factors [27]. Therefore, this study was designed as a quasi-experimental field study with a waiting list control group and pretest-posttest design. This means that one part of the experimental group (ie, unit A) will receive the intervention first, while another part of the group (ie, unit B) waits for an additional 3 months before they can make use of the intervention. Thus, the second unit acts as a temporary control group.

Three types of research methods can be distinguished in this study: (1) a longitudinal web-based survey study, (2) an ecological momentary assessment (EMA) study, and (3) a process evaluation. After the baseline measures (T0) of the web-based survey study are recorded, the yet-to-be-developed intervention aimed at recovery during work will be implemented within the experimental group.

Figure 1 presents a flowchart of the study design and the measurement moments. To analyze the effectiveness of the intervention, follow-up measurements will be performed at 3 months (T1) and at 6 months (T2) after the implementation of the intervention. This timeline seems adequate as the primary study outcomes (recovery during work and short-term negative effects of shift work) are expected to change over a relatively short period of time. In addition, an EMA study will be carried out shortly after the implementation of the intervention to provide insight into the short-term within-person intervention effects. Finally, a process evaluation will be performed to determine the factors that may have either enhanced or mitigated the effectiveness of the intervention.

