### Statistical Analysis

First, intervention results will be analyzed by performing mixed model repeated measures analyses (multivariate analysis of variance; time*group interaction) on longitudinal survey data with the outcome measures at follow-up (T0-T1, T1-T2, and T0-T2 comparisons) as the dependent variables. Furthermore, the effectiveness of the intervention will be analyzed by applying multilevel analyses on data collected within the EMA study (before break-after break and before break-after shift comparisons). Data will be collected and analyzed at 3 levels: (1) day level, (2) employee level, and (3) work unit level. Dropouts will be documented and included in the data analysis to the point of dropout. Potential confounders or effect modifiers (eg, age, gender, chronotype) will be compared between the intervention and the waiting list control group by *t* tests for independent samples and chi-square tests. For all analyses, a two-tailed significance level of *P*<.05 will be applied. The multilevel analyses will be conducted using R and the mixed model repeated measures analyses will be performed using SPSS software (IBM Corp, Version 25.0). A detailed analysis plan will be developed prior to finalization of the dataset.

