### Study Strengths

The design of this study has several strengths. First, by making use of the PAR approach, stakeholders at all levels of the company are involved. This bottom-up involvement of the stakeholders will contribute to the commitment to the proposed interventions, which will likely translate into better overall intervention adherence and compliance. Moreover, it allows the target group to participate in the development and implementation of the intervention. This approach will stimulate problem ownership and commitment at all levels of the organization and has the potential to contribute to organizational sustainability [29], for which the interventions are more likely to have the proposed impact [28]. Another strength of the study design is that the timeline for the experimental unit allows us to compare the short-term intervention effects (T1) with the long-term effects (T2). In addition, the intervention development is conducted in a similar way in both the departments, but the eventual workplace interventions can differ. As a consequence, we can compare different solutions on similar proposed outcomes, further contributing to both theory and evidence-based practice [54]. In addition, to determine the effects of the workplace intervention, we use a rather unique data triangulation. Next to group-level outcome measurements with a web-based questionnaire, EMA measurements are used to gain insight into the working mechanisms of the intervention and to determine the influence of the type of recovery strategy chosen, the time of day, the type of shift, and intraindividual differences. Moreover, a process evaluation will be performed in order to gain more insight into what aspects of the intervention work for whom and why [48]. The process evaluation outcomes are assessed qualitatively (ie, group interviews, observations, data logs) and quantitatively (ie, self-reported measures in digital surveys) and whenever possible, complemented with objective organizational data (eg, sickness absence registration).

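### Of the three listed time*group comparisons only T0-T1 sets intervention against no intervention; T0-T2 compares two treated units and cannot show effectiveness

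*Protocol article*

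**What the plan says.** The Statistical Analysis section states that "intervention results will be analyzed by performing mixed model repeated measures analyses (multivariate analysis of variance; time*group interaction") on the longitudinal survey data, "with the outcome measures at follow-up (T0-T1, T1-T2, and T0-T2 comparisons) as the dependent variables". All three comparisons carry the same description and the same two-sided 5% level. None is named as the effectiveness test, and no sign or reading is given for any of them.

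The Quasi-Experimental Field Study section sets the exposure pattern. It was a precondition of the organization that "both units would receive the intervention". Unit A starts first, while "unit B) waits for an additional 3 months before they can make use of the intervention". The section concludes that "the second unit acts as a temporary control group". T1 is at 3 months and T2 at 6 months after implementation. The Web-Based Survey section gives T0/T1 as pretest and T1/T2 as posttest, which fits unit B starting after T1.

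Study Strengths says that the timeline for the experimental unit "allows us to compare the short-term intervention effects (T1) with the long-term effects (T2"). The Conclusions of the Abstract also say that long-term effects will be evaluated.

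**The concern.** A time*group interaction estimates an intervention effect only over an interval in which one group is exposed and the other is not. That describes T0 to T1. From T1 to T2 unit B crosses over, and across T0 to T2 both units go from unexposed to exposed. The same model term therefore answers three different questions, yet the plan presents all three as analyses of intervention results.

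Two things are at stake. An intervention that works equally well in both units, and keeps working, would produce one positive, one negative and one null interaction, and the plan gives no guidance on reading that set. In addition, the long-term effect is presented as a design strength although no untreated unit remains at T2. The Quasi-Experimental Field Study section itself says that a control group is needed to separate the intervention from other change over time.

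**Working it through.** **Inputs**
- Exposure at T0, T1, T2: unit A 0, 1, 1; unit B 0, 0, 1 (Quasi-Experimental Field Study; Web-Based Survey). Figure 1 is not shown, so the timing comes from the text.
- Tested term, comparisons and alpha: time*group; T0-T1, T1-T2, T0-T2; 0.05 two-sided (Statistical Analysis).
- Sample size: Cohen f = 0.15, 37 per group, power 0.80; expected 150 × 0.75 / 2 = 56.25, so 56 per group (Sample Size).
- Assumption: within-person correlation rho = 0.5 at equal variances. The article gives no correlation.

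**1. The plan's own figure.** For a within-between interaction with k groups, m times and N subjects in total, lambda = f²·N·m/(1 − rho), with df (k − 1)(m − 1) and (N − k)(m − 1). With k = 2, m = 3, N = 74: lambda = 0.0225 × 74 × 3 / 0.5 = 9.99, df 2 and 144, power 0.806. This reproduces 37 per group. With m = 2 the requirement is 45 per group. The stated figure thus fits a three-wave interaction if rho is 0.5.

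**2. What each contrast estimates.** Let a1 and a2 be unit A's effects at T1 and T2, and b2 unit B's effect at T2. Assume the two units would otherwise change in parallel. The A-minus-B differences, apart from a constant, are 0 at T0, a1 at T1 and a2 − b2 at T2.
- T0-T1: a1
- T1-T2: (a2 − a1) − b2
- T0-T2: a2 − b2

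| Scenario | T0-T1 | T1-T2 | T0-T2 |
|---|---|---|---|
| Equal, sustained effect d | +d | −d | 0 |
| A grows to 1.5d | +d | −0.5d | +0.5d |
| A wanes to 0.5d | +d | −1.5d | −0.5d |
| B gains only 0.5d | +d | −0.5d | +0.5d |
| No effect | 0 | 0 | 0 |

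T0-T2 has the same expected value under an equal sustained benefit of any size as under no effect.

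**3. Size.** A change score has variance 2(1 − rho) = 1 SD². With 56 per unit the interaction has standard error √(2/56) = 0.189 SD. For a two-group, two-wave interaction f = d/4, so the plan's f = 0.15 corresponds to d = 0.6 SD. Then 0.6/0.189 = 3.17 and power is about 0.88 for T0-T1. It is the same for T1-T2, with a negative estimate. For T0-T2 under an equal sustained effect the rejection rate is alpha. Simulations of 20,000 trials per setting (rho = 0.5) gave:

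| d (SD) | n per unit | T0-T1 | T1-T2 | T0-T2 |
|---|---|---|---|---|
| 0.3 | 37 | 0.24 | 0.25 | 0.05 |
| 0.3 | 56 | 0.35 | 0.35 | 0.05 |
| 0.5 | 37 | 0.56 | 0.56 | 0.05 |
| 0.5 | 56 | 0.75 | 0.75 | 0.05 |

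More subjects do not raise the last column.

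**4. When T0-T2 is not null.** If the units' T2 effects differ by 0.3 SD (n = 56), 0.3/0.189 = 1.59 and power is about 0.35; at 0.6 SD it is 0.88. What is then detected is a difference between the units' interventions or exposure times.

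**5. Joint three-wave test.** For differences 0, d, 0 with d = 0.6, f = 0.6 × √(1/18) = 0.141, lambda = 0.02 × 112 × 3 / 0.5 = 13.44, df 2 and 220, power about 0.91. A joint interaction test would detect an equal sustained benefit, although it does not say which interval carries it.

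**The case against.** A reader might infer that a null T0-T2 interaction would be reported as no effect, or a negative T1-T2 interaction as harm. The article does not say so. It gives no reading rule and defers detail to an analysis plan still to be written. The pretest and posttest pairing, and the statement that "the second unit acts as a temporary control group", suggest that the authors know each unit has its own before-after window.

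A reader might also infer that the T0-T2 test always has power equal to alpha. That holds only for equal, sustained effects. Study Strengths allows the interventions to differ by unit and wants to compare them, so a T0-T2 interaction has a legitimate use there. Study Limitations expects that benefit may come late.

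Further, the sample size fits a three-wave interaction, so one joint model may already be intended, and the short- versus long-term comparison is confined to the experimental unit.

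These points limit the concern but do not remove it. The article already fixes the tested term and the three comparisons and describes them alike, so this is not merely detail left to a later plan. The between-unit use of T0-T2 is not stated where the comparison is listed, and it sets about 6 months of exposure against about 3. Confining the long-term claim to unit A confirms that it has no control.

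**Conclusion.** The concern holds in a limited form. Only the T0-T1 interaction compares intervention with no intervention. T1-T2 carries unit B's effect with reversed sign plus any further change in unit A. T0-T2 cannot show effectiveness: it is zero for an equal sustained effect of any size and otherwise mixes intervention content with duration. The long-term effect at T2 is an uncontrolled change within unit A.

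The contrast algebra assumes parallel change in the two non-randomized units apart from the intervention, and unit B starting after T1. The power figures also rest on the assumed rho = 0.5 and on an equal, sustained effect.

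The documents do not support the stronger conclusion that the study cannot show an effect. The T0-T1 test is planned, valid in form, and has power of about 0.88 at d = 0.6 SD with 56 per unit. This should be fixed before analysis, but it is not a fatal fault.

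**What to change.** In the Statistical Analysis section and the analysis plan to follow:
- Fit one model on all three waves and name the T0-T1 time*group contrast as the effectiveness test.
- State that the T1-T2 contrast carries unit B's effect with reversed sign, plus any further change in unit A.
- Report T0-T2 as within-unit change, labelled uncontrolled. Label any between-unit T0-T2 interaction as a comparison of the two units' interventions and exposure durations.
- Reword the long-term claim in Study Strengths and in the Conclusions of the Abstract to match.

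A pooled estimate with a time-varying exposure indicator (A: 0, 1, 1; B: 0, 0, 1) and fixed effects for unit and wave may be added, but only as a sensitivity analysis. Under compound symmetry its variance factor is 1 + ¼ + ¼ = 1.5 against 2 for T0-T1 alone, a 25% reduction; at d = 0.5 SD and n = 56, power rises from about 0.75 to 0.86. That gain requires the same effect in both units and no change with exposure time, which Study Strengths and Study Limitations call into question.

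The cost is analysis-plan wording, one recoded variable if the sensitivity analysis is added, and a weaker long-term claim. No new data are needed.

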#### EMA

During the intervention period, all employees will also be asked to participate in the EMA. EMA is a method for self-monitoring through the collection of self-reports on indices of behavior, cognition, or emotions in near real time in the daily lives of the participants, often through digital devices [42-44]. The smartphone-based questionnaire app allows us to digitally collect daily life momentary assessments of changes in employees’ levels of fatigue and recovery behavior, in relation to momentary context and activity. As such, it provides insight into the short-term, within-person mechanisms linking fatigue and recovery with short-term intervention effects. Event-contingent data collection protocols will be used, indicating that data entry takes place when a predefined event occurs [45,46]. The predefined event in this study is the formal work break. Participants will be asked to fill the data in the EMA app for a period of 14 consecutive days (1) directly before taking a work break, (2) directly after taking a work break, and (3) directly after the end of their shift. Each measurement moment will take about 1-2 minutes. In alignment with organizational management, we chose a period of 14 days to ensure enough day-level data points (despite rotating shift schedules and possible dropouts) without overburdening the participants. The use of the intervention, however, can continue after data has been collected.

Table 1 shows the variables that will be measured. The information provided will give insight into the effectiveness of the different recovery strategies (eg, relaxation and activation) and the influence of work break control, shift types, and personal characteristics (eg, age, chronotype, job position) on recovery outcomes. The start of the 14-day EMA period will be communicated through (1) the app via prompts, (2) the manager of the specific unit, and (3) through communication at the workplace (eg, posters, newsletters).

**Table 1 table1:** Variables retrieved through EMA.

Variable	Items	Questionnaire	Before break	After break	After shift
Shift type	1	What shift are you working today?	✓		
Sleepiness	1	Karolinska Sleepiness Scale [47]: scored on a scale from 1 (extremely alert) to 10 (very sleepy, difficulty in staying awake)	✓	✓	✓
Stress	1	Self-developed: “How do you currently feel?” scored on a visual analog scale (ranging from “stressed” to “relaxed”)	✓	✓	✓

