Need for work break	1	Self-developed: “To what extent are you in need of a work break right now?” scored on a scale ranging from 1 (not at all) to 10 (to a great extent)	✓		
Detachment from work	3	Based on de Jonge et al [33]: scored on a scale ranging from 1 (completely disagree) to 10 (completely agree)		✓	
Recovery activities	2	Self-developed: “During this work break, I spent my time mainly…”. 1 item scored with 3 answering categories: 1 (on activation activities such as walking, exercising, playing a game); 2 (on relaxation activities such as sitting, reading, listening to music, and power nap); and 3 ((other activities (please specify)) 1 item scored with 2 answering categories: 1 (alone) and 2 (with others).		✓	
Control	1	Self-developed: “I was able to decide for myself how to spend my time during this work break” scored on a scale ranging from 1 (completely disagree) to 10 (completely agree)		✓	
Work break satisfaction	1	Self-developed: “I am satisfied with the way I spend my time during this work break” scored on a scale ranging from 1 (completely disagree) to 10 (completely agree)		✓	
Level of recovery	1	Based on Demerouti et al [20]: “At this moment, I feel sufficiently recovered” scored on a scale ranging from 1 (completely disagree) to 10 (completely agree)		✓	
Productivity	1	Self-developed: “To what extent were you able to work productively during this shift?” scored on a scale ranging from 1 (not at all) to 10 (a great extent)			✓
Safety	1	Self-developed: “To what extent were you able to work safely during this shift?” scored on a scale ranging from 1 (not at all) to 10 (a great extent)			✓

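### The EMA before-to-after comparisons are presented as a test of intervention effectiveness, but as stated they measure the effect of taking a break or of time on shift

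*Protocol article*

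**What the plan says.** All references are to the protocol article.

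- **Purpose and contrasts (Statistical Analysis).** After the survey analysis, which has a time-by-group interaction, the section says that "the effectiveness of the intervention will be analyzed by applying multilevel analyses on data collected within the EMA study". In parentheses it names "before break-after break and before break-after shift comparisons". It continues: "Data will be collected and analyzed at 3 levels: (1) day level, (2) employee level, and (3) work unit level". A detailed analysis plan is to follow before the dataset is final.
- **Timing (Quasi-Experimental Field Study; EMA).** The design section says "an EMA study will be carried out shortly after the implementation of the intervention". The EMA section says "During the intervention period, all employees will also be asked to participate in the EMA", for one period of 14 consecutive days. No EMA wave before the intervention is described.
- **Trigger (EMA).** "The predefined event in this study is the formal work break".
- **Content (EMA, Table 1).** The activity question separates activation, relaxation and other (with free text), and alone from with others. No item asks whether one of the introduced practices was used.
- **Aim as worded elsewhere.** The EMA section expects to learn how well different recovery strategies work. Study Strengths presents EMA as a way to understand working mechanisms.

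**The concern.** Both EMA contrasts compare two moments in the same person's same shift. A worker who takes an ordinary break, with no new practice in it, may well feel less sleepy or less stressed afterwards. Sleepiness can also drift over a shift for reasons unrelated to any intervention. The stated contrasts absorb both effects in full and contain no term that removes them.

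Research question 2 asks how effective the intervention is. If the EMA result is reported under the label that Statistical Analysis gives it, a significant change could be taken as evidence on that question even if the intervention added nothing. A later analysis plan can add model terms, but it cannot supply an exposure item or a pre-intervention wave that was not collected.

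**Working it through.** **Step 1. Which outcomes can enter a before-to-after comparison.** From the ticks in Table 1:

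| Variable | Before break | After break | After shift |
|---|---|---|---|
| Sleepiness | yes | yes | yes |
| Stress | yes | yes | yes |
| Need for a break | yes | no | no |
| Detachment | no | yes | no |
| Level of recovery | no | yes | no |
| Productivity, safety | no | no | yes |

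Shift type is asked once, before the break. Activity, control and satisfaction are asked only after it. Only sleepiness and stress have a value before the break and a later one. The EMA section says the app captures changes in "levels of fatigue and recovery behavior, in relation to momentary context and activity". Table 1, however, has no item labelled fatigue (sleepiness is the nearest), and the recovery item, "At this moment, I feel sufficiently recovered", has no before-break value.

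**Step 2. What the contrast estimates.** Write the mean change from before to after as

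change = b + d + x,

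where b is the effect of any break, d is drift with time on shift, and x is what the intervention adds. With EMA only after implementation and no record of use, the stated contrast estimates the sum. Testing it against zero is a test of x only if b + d = 0.

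**Step 3. How often that would mislead if x = 0.** The documents give no EMA sample size, variance or break effect, so these inputs are assumptions:

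- n = 56 employees, borrowed from the survey calculation in Sample Size (150 × 0.75 / 2 = 56.25);
- 8 recorded breaks per person;
- between-person SD of change 0.5 and within-person SD of change 1.5.

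The two-tailed 0.05 level comes from Statistical Analysis.

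SD of a person's mean change = √(0.5² + 1.5²/8) = √0.53125 = 0.729. Standard error = 0.729/√56 = 0.0974. The noncentrality is the ordinary-break change divided by 0.0974, and the critical value is 2.004.

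| Ordinary-break change (points) | Noncentrality | Before-after test significant (2,000 simulated studies) |
|---|---|---|
| 0 | 0 | 5% |
| 0.1 | 1.03 | 17% |
| 0.25 | 2.57 | 71% |
| 0.5 | 5.13 | 99.7% |
| 1.0 | 10.27 | 100% |

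In the same simulation, a contrast of the change between two units, one exposed and one not, was significant in 4–5% of studies throughout. That holds because the simulation gives both units the same ordinary-break effect, which the real units need not share.

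On a standardized scale, an ordinary-break change of 0.5 SD of the person-mean change gives noncentrality 0.5 × √56 = 3.74 and a rejection probability of about 0.96.

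These are one-sample tests on person means, not the planned multilevel model. They show the direction of the problem and do not forecast this study's result.

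**The case against.** The strongest reply has five parts.

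1. **Work unit is a named level of analysis.** Unit is recorded at baseline, and one user account links survey and EMA data, so exposure status could be attached to every EMA record. This stands in part. A reader might infer that the EMA data carry no exposure information at all, and the article does not support that. But no unit-by-moment contrast is stated. Whether unit B did EMA while still waiting may be in Figure 1, which is not visible here. And management chooses which of the two units waits, so such a contrast would be confounded with unit.

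2. **Model terms belong in the analysis plan.** Agreed, and a missing interaction term alone would be no finding. What remains is the stated purpose set against the stated contrasts, and data that no plan can recover if they were not collected.

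3. **EMA is not the main test.** Agreed. The survey's time-by-group interaction is, and other sections treat EMA as a study of mechanisms. A reader might infer that the authors will report a break effect as an intervention effect. The article does not commit them to that; its wording allows it.

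4. **Recovery is not lost to EMA.** Also right. Detachment describes the break itself and has no meaningful earlier value. Level of recovery can be modeled as an after-break outcome against activity type, adjusted for need for a break. Recovery is outside the before-to-after comparison, not outside the EMA analysis.

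5. **The activity item, with its free text, is a proxy for use.** Only weakly. Sitting, reading or walking in an ordinary break fits the same codes.

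**Conclusion.** The point holds in this form: the EMA comparisons named in Statistical Analysis contain no stated intervention-versus-no-intervention term, so a before-to-after change cannot by itself be called intervention effectiveness. The bias, if it is read that way, equals the whole ordinary-break effect plus any drift over the shift. Under the assumed inputs, the chance of a significant result with no intervention effect runs from 17% to 100% for ordinary-break changes of 0.1 to 1.0 points. The size is uncertain because those inputs are not in the article; the mismatch between purpose and contrast does not depend on them.

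The survey analysis against the waiting-list unit is untouched, and EMA remains suitable for comparing recovery strategies and describing break processes.

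**What to change.** **Wording, available now.** In Statistical Analysis, describe the EMA analysis as one of break processes and recovery strategies, in line with the EMA section and Study Strengths. Leave the effectiveness claim to the survey's time-by-group interaction. Bring the mention of within-person intervention effects in the design section into line. The cost is a more modest claim for EMA.

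**For any EMA period not yet run.**
- Add one yes/no after-break item on whether an introduced practice was used in that break.
- Optionally, ask the existing recovery item ("At this moment, I feel sufficiently recovered") before the break as well.
- Make the tested parameter the moment-by-exposure interaction. State that use is self-chosen and so confounded by need for a break; the need item already in Table 1 allows partial adjustment.

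This costs one or two extra taps per entry.

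**Not recommended as the main remedy.** An EMA fortnight in unit B during its waiting period would give a concurrent comparison, but it appears no longer possible. Results reports first follow-up data collected in November to December 2019, and the wait lasts 3 months. An additional EMA period would also work against the 14-day limit, which was agreed with management to contain participant burden.
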